#### New BI

Referring to other blind studies, if the calculated confidence interval of the new BI includes zero, we will consider the blind method to be successful in this study.

Currently, we have not any additional analyses due to smaller sample sizes in each group.

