### Study design

This study is a two-center, randomized, sham-controlled, blinded patient and evaluator, parallel clinical trial. Our study will show if it is feasible to arrange patients randomly in EA trials of WM after stroke. The results of the study will be used to sample size calculation to provide a basis for subsequent research.

Sixty-six post-stroke patients will be recruited to participate in the trial. Before the experiment begins, the doctor will provide specific information about the trial to patients both orally and in writing. All patients will voluntarily sign an informed consent provided by the attending doctor. The informed consent was approved by the ethics committee before the formal experiment begins. All patients will be screened according to eligibility criteria. Sixty-six post-stroke patients will be randomly divided into theta-EA group, gamma-EA group, and sham-EA group according to the ratio of 1:1:1. The EA treatment and evaluation did not perform simultaneously. The evaluation will be performed the day before the intervention. The second evaluation is at least 2 h after the last intervention. All patients will receive an intervention that lasts for 4 weeks (30 min a day, 5 days a week, Monday to Friday).

Considering that the focus of this experiment is to explore the effects of EA at different frequencies on WM, patients in three groups will receive EA at two same acupoints in the head: Baihui (GV20) and Shenting (GV24). The frequency of the three groups of EA is selected as follows: 6 Hz (theta-EA), 40 Hz (gamma-EA), and no current through the electrodes (sham EA). The overall schematic diagram and schedule for the study are respectively shown in Figs. 1 and 2.

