#### Sham-EA group

The acupuncture points and operation procedures of the sham stimulation group were consistent with those of the other two groups. The only difference from the other two groups is that the electrode connected to the needle body is actually in a no-current state [30]. The details are as follows: (1) in the sham-EA group, a special wire which cannot be powered was used, although its appearance is not different from other ordinary wires; (2) visually, the sham-EA group looks the same as the two observation groups; (3) the EA device is placed behind the patient to ensure that the patient does not know the specific frequency parameters of the intervention; and (4) when the patient is undergoing intervention, the researcher will accompany the patient to ensure that the patient looks forward and stays still in a quiet state.

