##### New blind index

Patient and evaluator blindness will be assessed separately with the new BI [29]. They will be asked which group they think they belong to and choose one of the following answers: verum-EA group, sham-EA group, or unknown. The new blind index is scaled to intervals of − 1 to 1. Among them, 1 means there is no blind method at all, 0 means completely blind method, and − 1 means the opposite guess, which may be related to unblinding.

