### Sample size calculation

The primary endpoint was the difference of accuracy (d`) scores respectively at baseline and endpoint between the three groups (gamma-EA group, theta-EA group, and sham-EA group) in the 1-back test for patients with post-stroke. Since we did not have enough previous research as the basis for our estimated sample size, we chose the data collected in the previous pre-experiment to calculate the sample size required for this experiment. The null hypothesis is that *μ*_*i*_ = *μ*_*j*_ = *μ*_*t*_, while the alternative hypothesis is *μ*_*i*_ ≠ *μ*_*j*_ ≠ *μ*_*t*_, where *μ* is the mean difference and *i*, *j*, and *t* denote the sham-EA, gamma-EA, theta-EA group, respectively. Our pre-experimental results of 1-back accuracy (d`) scores show that after treatment, the d` values of the gamma-EA group (2.48 ± 0.32) and the theta-EA group (2.02 ± 0.53) are improved compared with the sham-EA group (1.88 ± 0.60). Using the sample size calculation formula for comparing the average of multiple independent samples in the parallel design, under the assumptions of α of 0.05 and (1-β) of 0.8, a sample size of 18 per group has been calculated. Considering a 20% dropout rate, a total of 66 patients will be enrolled in the trial (22 per group). The specific calculation formula is as follows [38]: *n* = λ/Δ

$$ \Delta =\frac{1}{\sigma^2}\sum \limits_{i=1}^K{\left({\mu}_i-\overline{\mu}\right)}^2\kern0.5em \overline{\mu}=\frac{1}{k}\sum \limits_{j=1}^k{\mu}_j $$

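### The blinding rule counts any blinding-index interval that includes zero as success, so moderate unblinding often passes in arms of 18 to 22, and zero can mislead if blinded patients lean towards guessing verum

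*Protocol article*

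**What the plan says.** The rule is in the Protocol article, Statistical analysis, New BI: "if the calculated confidence interval of the new BI includes zero, we will consider the blind method to be successful in this study". The section sets no largest acceptable index.

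Secondary outcome measures, New blind index, gives the scale: "1 means there is no blind method at all, 0 means completely blind method, and − 1 means the opposite guess". Respondents "choose one of the following answers: verum-EA group, sham-EA group, or unknown", so theta and gamma patients share one correct answer. The same section says "Patient and evaluator blindness will be assessed separately with the new BI".

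Under Study design, patients are "randomly divided into theta-EA group, gamma-EA group, and sham-EA group according to the ratio of 1:1:1", which is 2:1 for verum against sham. Under Sample size calculation, "a sample size of 18 per group has been calculated", raised to 22 for dropout. Under Sham-EA group, the stated difference from verum is that "the electrode connected to the needle body is actually in a no-current state".

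**The concern.** An interval that includes zero shows only that the data are compatible with no unblinding. It does not show that unblinding is small. With no upper bound, the rule rewards imprecision: a wide interval around a sizeable index passes, and a narrow interval around the same index does not.

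Zero as the sole reference raises a second difficulty. Two of three patients are in a verum arm and both verum arms map to one answer. If blinded patients lean towards guessing verum, the index moves above zero in verum and below zero in sham although nobody has learned anything about allocation.

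Sham carries no current while verum does, so any difference in sensation could reveal allocation. A success label that moderate unblinding often earns would give the verum-versus-sham comparison support that the data do not provide.

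**Working it through.** **Inputs.** From the Protocol article: three answers, a scale from -1 to 1, 1:1:1 allocation, 18 per arm before dropout and 22 enrolled. Assumed, because the article does not state them: the index is calculated within an arm, its interval is a two-sided 95% Wald interval, and 0% to 25% of respondents answer 'unknown'.

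**The plan's own figure.** The rule itself carries no number. The arm size that sets its precision can be reproduced. The pilot means 1.88, 2.48 and 2.02 have a sum of squared deviations of 0.1971. With SD 0.60, the largest of the three pilot SDs (the article does not say which was used), Δ = 0.1971/0.36 = 0.547. With λ = 9.635 (2 df, alpha 0.05, power 0.80), n = 9.635/0.547 = 17.6, so 18. Then 18 × 1.2 = 21.6, so 22.

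**Formulas.** BI = P(correct) - P(incorrect); variance = [P(correct) + P(incorrect) - BI²]/n; interval = BI ± 1.96 × SE.

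**Largest observed index that passes, no 'unknown' answers.**
- n = 22, 15 correct: BI = 8/22 = 0.364; SE = √[(1 - 0.132)/22] = 0.199; lower limit 0.364 - 0.389 = -0.03. Passes. With 16 correct, 0.455 - 0.372 = 0.08. Does not pass.
- n = 18, 12 correct: BI = 6/18 = 0.333; SE = √[(1 - 0.111)/18] = 0.222; lower limit 0.333 - 0.436 = -0.10. Passes. With 13 correct, 0.444 - 0.414 = 0.03. Does not pass.

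**Probability that the interval includes zero**, enumerated exactly over the possible counts:

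| True BI | Correct, if no 'unknown' | n = 18 | n = 22 | n = 22, 25% 'unknown' | n = 44 (both verum arms pooled) |
|---|---|---|---|---|---|
| 0.2 | 60% | 78.5% | 84.0% | 77.9% | 73.8% |
| 0.3 | 65% | 64.4% | 69.7% | 58.2% | 48.1% |
| 0.4 | 70% | 46.5% | 50.6% | 34.3% | 22.2% |
| 0.5 | 75% | 28.3% | 30.1% | 13.7% | 6.3% |
| 0.6 | 80% | 13.3% | 13.3% | 2.6% | 0.9% |
| 0.7 | 85% | 4.2% | 3.7% | 0.1% | under 0.1% |

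The n = 18 and n = 44 columns assume no 'unknown' answers. The effect of precision shows between 22 and 44: at BI 0.4 the pass rate falls from 51% to 22%. The 18 column is not higher than the 22 column because counts are discrete; at n = 18 the Wald interval covers a true zero only 90% of the time.

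**Zero as reference.** Let p be the probability of answering verum, with no 'unknown' answers. In a verum arm BI = 2p - 1; in sham BI = 1 - 2p. For blinded patients p is the same in every arm.
- p = 1/2: BI = 0 in every arm, whatever the allocation ratio.
- p = 2/3: BI = +1/3 in verum and -1/3 in sham. The interval includes zero with probability 0.638 at n = 22 and 0.389 at n = 44. A fully blinded verum group is therefore denied the success label 36% of the time as a single arm and 61% if pooled. In sham, real unblinding that moved the index from -1/3 to 0 would be scored as complete blinding.

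In general BI(verum) + BI(sham) = 2 × (p in verum - p in sham). The difference in the proportion answering verum is therefore zero when guesses are unrelated to allocation, whatever p is.

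**The case against.** A reader might infer that small arms guarantee success despite clear unblinding. The figures do not support that: at 22 per arm a true BI of 0.6 passes 13% of the time and 0.7 about 4%. 'Unknown' answers and pooling both make the rule stricter. This limits the point to moderate unblinding, roughly BI 0.2 to 0.4.

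A reader might also infer that 2:1 allocation by itself makes zero the wrong reference. It does not, because an index calculated within an arm is unaffected by the ratio unless guesses follow it. The article does not say that patients know the ratio, and under Blinding the acupuncturist is to give patients no information about the treatment. The +1/3 and -1/3 values are therefore conditional. The 61% figure needs a further step, pooling theta and gamma, which the article does not state; the single-arm figure is 36%. Pooling also weakens the first complaint, so the two halves of the point should not be argued with different arm sizes as if both applied together.

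Finally, the verdict enters no efficacy analysis, patients and assessors are already to be assessed separately, and an interval is already to be calculated. This stands. It makes the issue one of how the result is described, but it does not rescue the rule. The article states the rule outright; it is not a detail left to an analysis plan.

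**Conclusion.** The rule is wrong as written. It takes non-rejection of BI = 0 as proof of blinding, with no bound on the unblinding it tolerates. Under the stated assumptions, two thirds of an arm guessing correctly is certified as successful blinding. At 22 per arm, true indices of 0.3 and 0.4 pass in about 70% and 51% of trials without 'unknown' answers, and in 58% and 34% with a quarter 'unknown'. Strong unblinding is usually caught.

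That zero can mislead is a secondary and conditional point, resting on guesses that lean towards verum.

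It would go too far to conclude that a positive primary result could not be interpreted. No efficacy test depends on the verdict, both theta and gamma deliver current so the no-current concern does not touch the contrast between them, and readers would still have the index and its interval. What is at stake is an unsupported claim of successful blinding attached to the verum-versus-sham comparisons.

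**What to change.** Delete the success rule under Statistical analysis, New BI. In its place:
- report the BI with its 95% interval separately for theta, gamma and sham, for patients and for assessors;
- add the verum-minus-sham difference in the proportion answering verum, with its 95% interval;
- interpret the verum-versus-sham results in the light of these estimates, without a pass or fail label.

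Replacing the rule with a pre-set upper bound is sound in principle but out of reach at this size. With a true BI of 0 and no 'unknown' answers, 80% power for the upper 95% limit to fall below a margin needs ((1.96 + 0.8416)/margin)² per arm: 197, 88 or 50 for illustrative margins of 0.2, 0.3 or 0.4. At 22 per arm the half-width at BI = 0 is 1.96/√22 = 0.42. This trial can estimate unblinding but cannot demonstrate its absence.

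The cost is a change of wording and one table from answers already collected. The sponsor gives up an automatic statement that blinding was successful.

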### Patient safety

Adverse events attributable to the EA may include discomfort or bruising at the sites of needle insertion, nausea, or feeling faint. And in severe cases, the needle pain of EA may lead to transient hypertension, inducing recurrence of stroke or cerebral hemorrhage. The method that prevents these adverse events is as follows: (1) Researchers will maintain adequate communication with the patient before the intervention to ensure that the patient will be in a good state before the intervention, including blood pressure and emotional stability, non-hungry and enough rest; (2) During the intervention period, the researchers will pay close attention to the patient’s condition. If the patient feels any discomfort, the intervention will be stopped immediately and the adverse events will be dealt with accordingly. For example, when dizziness and headache occur, intervention should be stopped and the patient will be asked whether they have other discomforts. At the same time, the patient’s blood pressure and heartbeat should be measured immediately, and the attending physician will be notified to diagnose and treat the patient urgently, and if necessary, a corresponding imaging examination will be inspected to the patient; (3) after the patient’s condition is stable, the researcher will follow up patients to record and analyze the causes of adverse events in accordance with the requirements of ethics and clinical trials and discuss prevention plans to reduce the incidence of such adverse events as possible. Any medical occurrence after inclusion (not necessarily caused by the intervention) will be recorded on the CRF and on a progress protocol. This report will be sent to the ethics committee as a safety report. Serious adverse events will be reported to the ethics committee, coordinating center, steering committee, and sponsor immediately, and all participating will be informed by the sponsor, which is the Shanghai Municipal Development Office of Traditional Chinese Medicine. Researchers will try their best to prevent possible adverse events. And if the damage happened, the research team will provide treatment costs and corresponding financial compensation for the patient.

### Organization

Members of the coordinating center include the director, information manager, database programmer, statistical analyst, project coordinator, and research assistants. The director oversees the scientific aspects of the study design. The information managers are responsible for the collection of data and other information and quality assurance activities. Database programmers are responsible for entering data into the database. Statistical analysts are responsible for data analysis. The project coordinators are responsible for study communications, training, and certification of clinical staff in trial procedures. Research assistants are responsible for assisting others. Members of the steering committee include the study chair, data coordinating center director, statistician, and clinical center directors. The responsibilities of the steering committee include the following: (1) review and approval of trial procedures, (2) resolution of technical or operational issues, (3) review of study progress and approval of major changes to the study protocol, and (4) oversight of publication of study findings. In this study, the responsibilities of the endpoint adjudication committee are included in the ethics committee and the data management team is included in the coordinating center. Therefore, there is no independent endpoint adjudication committee and data management team.

### Quality control

To ensure the treatments and assessment at a high standard, both the acupuncturist and the assessor have to provide a proven record of at least 2 years of clinical experience. All clinicians in this study will participate in a 3-day training course in the standard operating procedures provided by the author of the protocol. In this training course, the protocol will be explained and practiced during exercises and role-plays. The coordinating center, independent of the sponsor, will monitor source documents every 3 months. Whether the data is complete and accurate will be determined by the coordinating center. The regulatory binder which includes the protocol and all revisions of informed consent, case report forms, and the investigator’s agreements will be also up to date by the coordinating center.

## Discussion

WM disorder is a hidden dysfunction in post-stroke [4]. In traditional rehabilitation training, there is no effective rehabilitation program for working memory [40, 41]. Acupuncture has an exact effect on the improvement of cognitive function after stroke [42, 43]. However, there is no clear evidence on whether EA can improve WM and the choice of frequency is unclear. Therefore, we design a double center in a random, sham comparison and blinded of patient and evaluator, parallel clinical trial to observe the effectiveness of theta and gamma EA therapy and sham EA therapy for WM.

### Acupuncture points selection

In this study, we chose two acupoints—“Baihui” (GV20) and “Shenting” (GV24), which are situated on the Du meridian—for our study. In the TCM theoretical system of acupuncture, the Du Meridian is the center of the brain and is closely related to the mind [44]. Baihui (DU 20) and Shenting (DU24) are closely related to brain function and are widely used in the treatment of mental and emotional illnesses [45]. Baihui (DU20) is located at the highest point of the head, where all the yang meridians meet. Baihui (GV20) has the functions of clear the mind, lift the spirits, and promote resuscitation in acupuncture [46]. Shenting (DU24) is located on the anterior median line of the head and is also an important acupoint for the Du Meridian. The efficacy of Shenting (DU24) is similar to Baihui. These two acupoints are often used in combination in clinical practice [12]. In modern times, many studies using animal models of stroke have revealed that acupuncture at the Baihui (DU20) and Shenting (DU24) acupoints can ameliorate the learning and memory deficits of rats with cerebral ischemia/reperfusion (I/R) injury [47, 48]. Effects of the treatment include the following: (1) alleviate the damage of brain edema caused by cerebral ischemia [49], (2) increase the expression of cell division cycle [50], (3) increase cerebral perfusion of the cerebral cortex [51], and (4) increase the plasticity of neuroblast and enhancing the proliferation of cell [52].

### Outcome measurements selection

*N*-back task, as the primary outcome, is one of the traditionally been used paradigms to explore the neural basis of WM and executive function (EC) [53]. Neuropsychological studies show EC (including shifting, updating, and inhibition) is a core component of WM [54], unlike other simple storage tasks, such as forward digital span task [55]; *n*-back task is regarded as a typical task loading on WM updating [56]. In *n*-back task, participants need to decide whether the current stimulus is the same as the stimulus they saw *n* steps back. The larger the value of *n*, the higher the difficulty level of the test [57, 58]. In the pre-experiment, we booked 9 patients with cerebral infarction and randomly assigned them to the theta-EA group, gamma-EA group, and sham-EA group. The intervention parameters and course of treatment are consistent with this experiment. Before intervention, patients were evaluated 0-back, 1-back, and 2-back. It was found that 6 subjects had difficulty performing 2-back, so only 0-back and 1-back were evaluated after the intervention. The results showed that 0-back has the ceiling effect. Thus, we choose 1-back to assess patients’ working memory. In addition to dealing with behavioral evaluations, analysis of the EEG signals is also an important aspect. Studies have shown that the different components of ERP are closely related to the information processing process of working memory [59]. For example, N2 is related to the maintenance of information [60], and P3 is related to the updating of information and allocation of attentional resource [61]. Hence, we recorded the task status of the patient’s EEG signals to explore the impact of the intervention scheme on the electrical activity of the cerebral cortex, including relative to sham.

### Limitation

There are some limitations in this protocol. First, because there are few clinical studies on working memory rehabilitation of patients after stroke, this study is based on the results of the pre-experiment to calculate the sample size. The sample size of this study is small, which is insufficient to conduct a comprehensive study. Second, previous acupuncture studies have often used body and scalp acupoints for post-stroke patients with cognitive impairments [62–64]. However, considering that this study will also observe the effect of EA on the electrical activity of the cerebral cortex, we will only use two scalp acupoints to reduce the interference caused by too many acupoints.

## Trial status

Ongoing recruitment.

Protocol version number V1, April 2020. Recruitment began on April 2020 and will be completed by June 2021.

## Data Availability

The datasets used and/or analyzed after completing the current study will be available from the corresponding author by reasonable requests.

## Abbreviations

WM: Working memory
EA: Electroacupuncture
MMSE: Mini-Mental State Examination
RBMT: The Rivermead Behavioral Memory Test
TMT: Trail Making Test
LOTCA: Loewenstein Occupational Therapy Cognitive Assessment Scale
MBI: Modified Barthel Index
new BI: New blind index
